**1. Background**

**1.1. Malaria as a cause of anaemia**

Malaria is a major cause of morbidity and mortality in children in sub-Saharan Africa. In Africa, malaria causes over a million deaths and many million episodes of illness each year in children less than five years-old. 1 Anaemia, caused by malaria and iron deficiency, is another leading cause of severe disease in children in Africa.2 Around 75% of preschool children in East Africa are anaemic 3 and anaemia in childhood is associated with impaired physical and mental development. 4 In areas of high malaria enedmicity the incidence and adverse effects of anaemia are most marked in the first 1-2 years of life. 5

Several studies have shown that iron supplementation increases the haemoglobin level in young children resident in malaria endemic areas.5,6 However, concerns have been expressed about the effect of iron supplementation on malaria.7 An increased incidence of malaria as a result of iron supplementation can occur under some circumstances, but there is a general consensus that the effect is not marked and is out-balanced by the beneficial effect of iron on anaemia. Daily iron supplementation given by mothers reduced the incidence of severe anaemia by 32% in infants in a highly malaria endemic area of Tanzania without increasing clinical episodes of malaria in children who received iron. 6 In this study, additional administration of malaria chemoprophylaxis ((weekly Deltaprim (pyrimethamine/dapsone)) led to a 57% reduction in severe anaemia and a 60% reduction in episodes of malaria. These results support iron supplementation for infants, even in malaria endemic areas, and suggest an important role for chemoprophylaxis.

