Lapdap. Lapdap (chloroproguanil/dapsone) is a new anti-folate anti-malarial based on a combination of two old and widely studied drugs. Lapdap has recently been through a full clinical evaluation and it is expected that the drug will be licensed in mid 2003. Studies conducted in Kenya in the 1980s and 1990s showed that this short acting drug combination was safe and effective. Clinical trials of Lapdap have recently been conducted in 1480 children in five African countries as part of the regulatory process. In each country, Lapdap was more effective than SP and in Kenya, Gabon and Malawi the difference between groups was statistically significant.29,30  Detailed safety observations were made; minor side effects were recorded frequently (some of these may have been due to the underlying malaria infection). Falls in Hb in children who were glucose-6-phosphate dehydrogenase deficient were recorded more frequently in children who received Lapdap than in those who received SP but no other significant side effects were recorded. In a separate open label study conducted in infants aged 3 – 12 months the drug was again shown to be safe and effective.29

A number of trials of Lapdap have been conducted in the proposed study area. 31,18 The most important, conducted in 1989/99, showed that 41/43 children who had failed treatment with SP responded fully to treatment with Lapdap.18 Thus, Lapdap is likely to be effective when used for IPTi in this area of Africa where levels of SP and AQ resistance are high.

Advantages of Lapdap as a potential drug for use in IPTi are that it is likely to be cheap and that its short action will diminish the chances of inducing resistance; its disadvantage is that a full therapeutic course requires drug administration over a period of three days.

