**Figure 2**. **Study design**

**Contact 0**: Infants attend EPI clinics for BCG and/or DPT & Polio1 vaccines

1. identification of eligible infants

2. provision of information about the study to the care takers

3. enrolment of eligible infants after obtaining informed consent

2 months

Approximate age

**Contact 1:** Infants return for DPT 2 and Polio 2 vaccines

1. random allocation to one of the study groups

2. administration of the first course of treatment

3. collection of blood samples for Hb and blood film and filter paper

4. appointment for contact 2 (DPT and polio 3)

Group 1

placebo

Group 2:

Mefloquine

Group 3:

Lapdap

Group 4:

SP

Passive surveillance at health facilities for side effects of drugs, clinical malaria, and anaemia until 24 months of age

**Contact 2**: Infants attend EPI clinic for DPT 3 & Polio 3 vaccines

1. completion of data forms and administration of the second course of allocated drug

2. appointment for contact 3 (measles vaccine)

**Contact 3**: Infants attend EPI clinic for measles vaccine

1. completion of data forms and administration of the third course of allocated drug
2. collection of blood samples for baseline measles serology
3. appointment for contact 4 (1 month after the date of contact 3)

**Contact 4**: (1 month after the date of contact 3)

Collection of blood samples for Hb, blood film, post vaccine measles serology, and anti-VSA antibody assay

1 months

3 months

9 months

10 months

**Contact 5**: (20% random sample)

Collection of blood sample for Hb and blood film

**Contact 6**: (20% random sample)

Collection of blood sample for Hb and blood film

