**4.3. Outcome measures**

*Primary outcome measures*

1. Incidence of clinical malaria: [(history of fever during previous 2 days or axillary temperature >37.5ºC) + parasitaemia of any density + absence of any other obvious causes of fever] during the period of 2-11 months of age

*Secondary outcome measure*

1. Mean Hb at 10-12 months of age (one month after the third course of IPTi)
2. Incidence of severe anaemia (Hb <7 g/dl) during the period of 2-11 months of age
3. Prevalence of parasitaemia at 10-12 months of age (one month after the third course of IPTi)
4. Incidence of clinical malaria [as defined above] during the period of 12-23 months of age.
5. Level and repertoires of plasma antibodies to *plasmodium falciparum* variant surface antigen (anti-VSA antibodies) at 10 and 18 months of age.
6. EPI serology
7. Prevalence of G6PD deficiency and human haemoglobinopathies.

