**4.5. Screening, enrolment and follow up procedures**

All infants attending the EPI clinics at the study health centres for BCG or DPT&polio 1 vaccination (**contact 0**) will be screened for eligibility for enrolment into the study. The study objectives and procedures will be explained to caretakers of the infants who are eligible and they will be given an information sheet to take home. After obtaining written consent, the following procedures will be carried out: (1) collection of digital photos for a photo ID card; (2) completion of an enrolment form which will contain information on identification, address and other details useful for follow up at home, socio-economic status, use of bednets and other malaria prevention measures, clinical history and signs and anthropometric indicators.

A list of study infants due for DPT/Polio 2 vaccination in each study EPI clinic on a given date will be generated from the enrolment database a week prior to the scheduled date. A member of the project team will visit the homes of these infants and remind them to attend the scheduled EPI clinic.

When the study infants return for DPT& Polio 2 (**contact 1**) the following procedures will be carried out: (1) allocation of infants to one the four arms of the study; (2) administration of the first dose of the study drug and dispensation of the remaining two doses of drug to be given at home; (3) collection of blood samples for Hb, malaria parasite and blood spot for genetic markers of drug resistance parasites; (4) advice given to the caretakers to bring their children to the health facility if the child becomes ill before the next scheduled visit.

In both study areas, the first 200 children will be followed up on day 7 post-administration of IPTi first course (**contact 1a**) and a finger prick blood sample will be collected for determination of haemoglobin and preparation of blood film.

A list of study infants due for DPT/Polio 3 vaccination in each study EPI clinic on a given date will be generated from the contact 1 database a week prior to the scheduled date. A member of the project team will visit the homes of these infants and remind them to attend the scheduled EPI clinic.

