All study infants will be encouraged to attend the study health facilities for any illness. At these visits a health questionnaire will be completed and temperature recorded using an electronic thermometer. A finger prick blood sample will be collected for Hb and malaria parasite and for detection of molecular markers of resistance from all infants attending the study health facilities for any illness that is clinically diagnosed as malaria. At the health centres one blood slides will be examined on the same day for deciding on appropriate treatment whilst the second slide will be read in the central laboratory to provide definitive diagnosis.

Children with proven or presumptive malaria will be treated according to the MoH guidelines for managing treatment failures following first line drugs. We have opted for the second line antimalarials instead of giving SP, the first line drug recommended by the MoH, because we believe that most of the break through infections will be in the SP and placebo groups and therefore a repeat dose of SP will not be appropriate in this setting where there is a high level of SP resistance.

To ensure that IPTi with any of the study drugs does not lead to a rebound in the incidence of severe malaria or anaemia during the second year of life all infants enrolled in the study will be followed until they reach the age of 24 months. During their second year of life, all episodes of possible malaria or anaemia in infants who present to health centre in the study area will be documented.

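### First-year illness visits take Hb only on a clinical diagnosis of malaria, so severe anaemia from other causes is under-ascertained and the severe-anaemia rate ratio is expected to lean towards the active arms

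*Protocol*

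**What the plan says.** - **Outcome (section 4.3).** Secondary outcome 2 is "Incidence of severe anaemia (Hb <7 g/dl) during the period of 2-11 months of age". No cause is specified.
- **Scope of surveillance (Figure 2).** "Passive surveillance at health facilities for side effects of drugs, clinical malaria, and anaemia until 24 months of age".
- **What every sick infant gets (section 4.9).** "At these visits a health questionnaire will be completed and temperature recorded using an electronic thermometer".
- **Who gets an Hb at an illness visit (section 4.9).** The sample for Hb and parasites is taken "from all infants attending the study health facilities for any illness that is clinically diagnosed as malaria".
- **Second year (section 4.9).** A recording rule begins: "During their second year of life, all episodes of possible malaria or anaemia in infants who present to health centre in the study area will". This sentence does name anaemia, but only after the first birthday, and it specifies no Hb test.
- **Causes of anaemia other than malaria.** Section 1.1: "Anaemia, caused by malaria and iron deficiency, is another leading cause of severe disease in children in Africa". Section 1.4: "Falls in Hb in children who were glucose-6-phosphate dehydrogenase deficient were recorded more frequently in children who received Lapdap" than in those given SP. Section 1.6 names haemolytic anaemia as a risk with both SP and Lapdap in G6PD-deficient patients.
- **Safety Hb (sections 4.5 and 4.8).** In both areas, "the first 200 children will be followed up on day 7 post-administration of IPTi first course", and a second 200 on day 7 after the third course. The DSMB reviews these data unblinded.

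**The concern.** The outcome is anaemia of any cause, but outside scheduled visits the measurement that defines it depends on a diagnosis of malaria. A pale or jaundiced infant in the first year whose illness is not judged to be malaria has no stated route to an Hb. Section 4.9 therefore does not deliver the surveillance that Figure 2 describes or that outcome 2 needs.

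The omission need not be neutral between arms. The active drugs are expected to reduce malaria, so they reduce the part of severe anaemia that is well detected. The under-detected part is unaffected by the drug or, with haemolysis, increased by it. Two things are at stake: the severe-anaemia comparison, and the chance of seeing drug-related anaemia, in a trial whose first objective includes safe use. An analysis plan cannot recover an Hb that was never taken.

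**Working it through.** **1. The plan's own figures.** Inputs are the severe-anaemia rates per child-year in Tables 6a and 6b: 0.16 / 0.08 / 0.12 (placebo / mefloquine / Lapdap or SP) in the low site and 0.39 / 0.20 / 0.30 in the high site. The formula is n = (1.960 + 0.842)² × (r1 + r2) / (r1 − r2)², with one child-year each.

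- Low site: 295 / 1,374 / 982, against 295 / 1,377 / 984 stated.
- High site: 129 / 669 / 393, against 129 / 670 / 393 stated.

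These reproduce. No stated number is wrong; the issue is how the events are found.

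**2. Where Hb is measured in the 2-11 month window (Figure 2, sections 4.5 and 4.8).**

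- Contact 1, about 2 months: all infants, at the visit of the first dose.
- Contacts 2 and 3, about 3 and 9 months: no Hb; contact 3 blood is for measles serology.
- Day 7 after courses 1 and 3: subsamples only; none after course 2.
- Contact 4, about 10 months: all infants.
- Contact 5, about 11 months: 20%.

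So no Hb is scheduled for most infants for about eight months, a span that contains all three courses. Section 4.8 expects about 200 Lapdap infants in the day-7 data. With (1,280 + 2,440) / 4 = 930 infants per arm and three courses each, there are about 2,790 Lapdap courses. Since 200 / 2,790 ≈ 7%, about 93% of Lapdap courses have no day-7 Hb.

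**3. Direction.** In the placebo arm let m be the rate of malarial severe anaemia and o the rate of other severe anaemia. Let r be the drug's rate ratio on malarial anaemia, h the rate of drug-caused anaemia, and d the share of non-malarial cases that still get an Hb, assumed equal across arms.

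- All-cause ratio = (m·r + o + h) / (m + o).
- Observed ratio = (m·r + d(o + h)) / (m + d·o).

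The derivative of the observed ratio in d has the sign of m[o(1 − r) + h]. This is positive whenever r < 1 and either o or h is above zero. So for any d < 1 the observed ratio lies below the all-cause ratio, in favour of the active arm. If fewer malaria visits also meant fewer incidental Hb tests on active drug, d would be lower in that arm and the shift would go the same way.

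**4. Illustration.** Tables 6a and 6b assume overall ratios of about 0.5 (mefloquine) and 0.75 (Lapdap or SP); here they are applied to the malarial part as r. The non-malarial share (10-50%), h (0 or 10% of the placebo rate) and d (0-0.5) are assumptions, because the protocol gives none of them. The ratios are the same at both sites.

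| r | Non-malarial share | h | All-cause ratio | Observed, d = 0 | Observed, d = 0.5 |
|---|---|---|---|---|---|
| 0.50 | 10% | 0 | 0.550 | 0.500 | 0.526 |
| 0.50 | 50% | 0 | 0.750 | 0.500 | 0.667 |
| 0.50 | 50% | 10% | 0.850 | 0.500 | 0.733 |
| 0.75 | 10% | 0 | 0.775 | 0.750 | 0.763 |
| 0.75 | 25% | 10% | 0.913 | 0.750 | 0.843 |
| 0.75 | 50% | 10% | 0.975 | 0.750 | 0.900 |

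For example, row five at the low site has m = 0.12, o = 0.04 and h = 0.016. The all-cause ratio is (0.090 + 0.040 + 0.016) / 0.16 = 0.913. At d = 0.5 the observed ratio is (0.090 + 0.028) / 0.14 = 0.843. Across the table the shift runs from about 0.01 (0.775 − 0.763) to 0.35 (0.850 − 0.500).

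**5. Rate difference.** Equally missed non-malarial cases cancel on this scale; drug-caused cases do not. In the same example the true difference is 0.16 − 0.146 = 0.014 per child-year, and the observed one at d = 0 is 0.12 − 0.09 = 0.030.

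**The case against.** Much can be said for the plan, and most of it stands as a limit on the point.

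- **Other sources exist.** Outcome 2 is not restricted to malaria visits, so a low Hb at contact 4, at contact 5 or on day 7 counts. Section 4.8 keeps records of transfusion for anaemia at the two hospitals, and Appendix 3 makes any hospitalisation a serious adverse event. A reader might infer that non-malarial severe anaemia is missed altogether. The documents support under-ascertainment only.
- **Lapdap haemolysis has its own safety component.** The day-7 Hb, the unblinded DSMB review, G6PD testing if Hb falls, and the DSMB's option to ask for more data are all in section 4.8. They are real safeguards, but they cover a subsample and one time point.
- **The trigger is not the malaria outcome.** The outcome requires parasitaemia; the trigger is a clinical judgement, and the sample that shows parasitaemia is taken because of it. In Tables 3 and 4, facilities with no laboratory recorded between 33% (408/1,232) and 87% (1,527/1,755) of under-five outpatient cases as malaria. Those figures are from 2002 and include facilities outside the trial, but they suggest that many febrile infants without malaria would be bled. This argues for a small bias.
- **The adverse-event form is not shown.** A reader might infer that it has no place for an Hb. The protocol says only that illness within 28 days is documented on it.
- **Large figures can be produced.** With no detection of non-malarial cases, a 20-50% non-malarial share and haemolysis of 0.01-0.03 per child-year, an observed ratio of 0.75 would stand for a true 0.86 to 1.06. That needs the extreme of zero detection and two inputs that the protocol does not give, so it is not an estimate.
- **The outcome is secondary, and weakly powered for Lapdap or SP against placebo.** It needs 1,377 and 670 per arm; 610 and 320 are planned. This lowers the stakes for those comparisons. It does not for mefloquine against placebo, which needs only 295 and 129.

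None of this supplies a first-year Hb trigger for suspected anaemia.

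**Conclusion.** The point holds, at moderate severity, for a secondary and safety outcome. Section 4.9 does not match section 4.3 and Figure 2: the only Hb trigger at first-year illness visits is a clinical diagnosis of malaria, while the outcome is severe anaemia of any cause. Between contact 1 and contact 4, cases that present without that diagnosis are under-ascertained, apart from those reached by the day-7 subsamples and the hospital transfusion records.

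The expected direction favours the active arms on the rate-ratio scale. It rests on the drugs reducing malarial anaemia and on non-malarial cases being less often tested. The size is unknown, since the non-malarial share, the haemolysis rate and the detection share are all absent from the protocol; the 0.01 to 0.35 range only shows how much depends on them. The primary outcome is unaffected, and so is mean Hb at contact 4, which is taken in all infants.

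**What to change.** Reconcile section 4.9 with section 4.3 and Figure 2. State in 4.9 that a finger-prick Hb is taken at any illness visit, at any age under surveillance, that is clinically diagnosed as malaria or as suspected anaemia (for example pallor or jaundice). Report severe anaemia overall and split by malaria diagnosis yes/no, so that the under-detected part can be seen. Taking Hb at other illness visits within 28 days of a course would strengthen the safety data further, but is more burdensome and optional.

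The cost is one sentence in 4.9, the matching clinic procedure, and some additional finger pricks in sick infants and microcuvettes. Section 9 already budgets a Haemocue for each study health centre. Table 8's 200 boxes of 100 cuvettes for $40,000 work out at about $2 per test (40,000 / 20,000).

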**4.10 Iron status**

From the stored blood samples, after breaking the code, 200 samples (collected at 10 months of age) will be selected randomly from the placebo group of children from each site for assessing the serum ferritin levels. Measuring serum ferritin levels is needed to assess the background level of iron deficiency in the study population.

**4.11. Evaluation of resistance to study drugs**

Comparison of the relative efficacies of short and long acting drugs would be confounded if there were major differences in the level of parasite resistance to the drugs under investigation. It is likely that both Lapdap and mefloquine will be highly effective in the study area but it is essential to confirm this. Thus, a subsidiary trial of efficacy of the study drugs for clearing asymptomatic parasitaemia will be carried out (see section 4.5). We opted to study the efficacy of the study drugs to clear asymptomatic parasitaemia instead of clinical malaria, because children with asymptomatic parasitaemia are often semi-immune to the parasite strain causing their infection and the parasite density is usually lesser in asymptomatic than in symptomatic infections. Thus different levels of efficacy may be obtained when asymptomatic or symptomatic infections are treated. This will be primarily a descriptive study. It is anticipated that parasite clearance by day 14 will be over 90% in the mefloquine and Lapadap treatment groups but much less in the SP group.

We expect a 10% loss to follow up at 24 months of age and so around 3340 children (low and high transmission area combined) would be screened for this sub-study. We assume that 20% of these children will have parasitaemia and thus 668 children would be allocated to mefloquine, lapdap, or SP treatment group. We assume efficacies of 90% at day 14 in children in the mefloquine and Lapdap groups, and 50% for children in the SP group, the study will have adequate power to estimate the efficacy of these drugs with acceptable level of confidence limits (95% confidence limits of efficacies of mefloquine and lapdap would be +/- 4% and that of SP would be +/- 7%.

Resistance to SP is linked strongly to mutations in the dihdyrofolate reductase (DHFR) and dihydropteroate synthase (DHPS) genes and resistance to Lapdap is probably also strongly related to mutations in these genes, although this has not been established so clearly. There are no definitive molecular markers for mefloquine resistance although some linkage to mutations in the *Pfmdr* gene has been described (24). In order to define the overall level of resistance to anti-folate drugs in the study area, DNA will be extracted from filter paper blood samples obtained from children in the control group who are parasitaemic when blood samples are collected at 10 months of age and tested for DHFR and DHPS mutations. These parasites will not have been subjected to selection by drugs given for IPTi and should reflect the overall pattern of resistance in the community. With a total of around 930 children in the placebo control and an overall parasite prevalence of 25% there should be around 230 samples available for molecular analysis. Information obtained on the background level of resistance to anti-folate drugs will allow comparisons to be made between the results of this trial and other trials of IPTi which have used, or are using, SP.

**4.12. Laboratory procedures**

**Haemoglobin**: capillary blood will be collected in a microcuvette and examined in a Haemocue machine to determine Hb.

**Malaria parasite**: Thick and thin blood smear made from capillary blood will be stained with Giemsa stain and examined under light microscope. To estimate the parasite density, parasites in thick film fields will be counted until 200 leukocytes have been counted an the parasite count will be multiplied by a factor of 40 to give parasites per µl of blood. All blood films will be read twice by individual observers. Discrepant findings will be reviewed by a supervisor and a consensus on positivity and density will be reached. A quality control system will be established to ensure the accuracy of blood film readings and Hb determinations.

**Drug Assays**: Mefloquine, dapsone and pyrimethamine concentrations will be measured in randomly collected urine samples obtained at three day follow-up visits using an HPLC method developed at LSHTM ([name], unpublished) which allows the detection of several anti-malarials in one chromatogram. Due to the problems of collecting urine from infants we will use blood spots collected on filter paper from finger or heel prick samples.

**Molecular markers**: DNA will be extracted from filter paper blood samples obtained from parasitaemic children and tested for mutations in DHFR and DHPS genes using standard PCR and SSOP techniques developed at LSHTM.40, as well as being tested for mutations in the G6PD gene and haemoglobin genes using a modified SSOP detection method developed at CMP, University of Copenhagen42.It is planned to undertake both chromatographic and molecular studies at the new laboratory being built at Bombo Hospital, Tanga on the edge of the study area with support from the Bill and Melinda Gates Foundation. This laboratory should be operational by the end of 2004. Measles antibodies will be measured by a standardised neutralisation assay at a central laboratory contracted by WHO to undertake serology for the consortium.

**Anti-VSA antibody assays**: Anti-VSA antibodies will be measured with a flow cytometric assay that allow the assessment of levels of plasma antibodies to a panel of *in vitro* cultured parasite isolates, some of which are commonly and others rarely recognized. Further antibody assays will be used including ELISA and adhesion-blocking assays. Levels of antibodies and the proportion of parasites recognized will be compared between treatment groups and analysed with respect to clinical protection with statistical regression models. We will compare the level and repertoire of anti VSA antibodies at 10 and 18 months of age, and the incidence of malaria in the second year of life between the study arms. We will include the following terms in a Poisson regression model to assess the effect to IPTi on immunity and clinical malaria: IPTi regime, level of anti VSA antibodies, age, sex, transmission levels and other potential confounders identified during the analysis as predictors and incidence of malaria as the outcome.

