**1.6 The influence of G6PD deficiency and human haemoglobinopathies**

Glucose-6-phosphate (G6PD) deficiency and human haemoglobinopathies, such as sickle cell trait and alpha-thalasseamia are (important) inherited genetic factors, which may influence the outcome of IPTi43,44. G6PD-deficient red blood cells are more susceptible to oxidative stress, and haemolytic anaemia more prone to develop in G6PD-deficient patients receiving antimalarial drugs such as SP and Lapdap45. By monitoring the prevalence of G6PD deficiency in the study population, it will be possible to predict the risk of haemolytic anaemia among the study participants treated with these drugs, and further to adjust for the effect of G6PD deficiency when analysing the effect of different IPTi drugs on the prevalence of anaemia. Furthermore, by testing for these genetic factors, which have been associated with innate resistance to malaria, it will be possible to adjust for their influence when assessing the possible influence of different IPTi drugs on malaria morbidity and acquired immunity.

1. **Objectives**

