2.2 Secondary objective

- To determine whether IPTi through the EPI interacts with the immune response to routine immunisations
- Assessment of the effect of G6PD deficiency and haemoglobinopathies on the outcome of IPTi.

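### Section 4.12 takes DNA for G6PD and haemoglobin-gene typing from parasitaemic children, which cannot give the study-population prevalence and genotype adjustment that the protocol promises

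*Protocol*

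**What the plan says.** One sentence in Section 4.12 (Molecular markers) reads "DNA will be extracted from filter paper blood samples obtained from parasitaemic children and tested for mutations in DHFR and DHPS genes" and, after naming the technique, continues "as well as being tested for mutations in the G6PD gene and haemoglobin genes". The grammatical subject is the same DNA. No other routine source of DNA for the host genes is given anywhere in the protocol.

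Three other places depend on this typing:

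- Section 1.6: "By monitoring the prevalence of G6PD deficiency in the study population, it will be possible to predict the risk of haemolytic anaemia". It also foresees adjusting the analyses of anaemia, malaria morbidity and acquired immunity for these genes.
- Section 2.2, a secondary objective: "Assessment of the effect of G6PD deficiency and haemoglobinopathies on the outcome of IPTi".
- Section 4.3, secondary outcome 7: the prevalence of G6PD deficiency and haemoglobinopathies.

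Two further passages bear on the sampling. Section 4.5 lists at contact 1 "collection of blood samples for Hb, malaria parasite and blood spot for genetic markers of drug resistance parasites", so a spot is planned for infants at first dosing, with parasite resistance as its stated purpose. Section 4.8 allows G6PD status to be determined, if necessary, in children of the day-7 haemoglobin safety sample whose Hb falls, and in matched controls.

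**The concern.** Restricting to parasitaemic children is right for DHFR and DHPS. They are parasite genes, and an uninfected child has nothing to type. G6PD and haemoglobin genes belong to the child, so the same restriction becomes a selection rule.

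The protocol gives both reasons why that selection matters. Section 1.6 describes the host factors as ones "which have been associated with innate resistance to malaria, it will be possible to adjust for their influence", so carriers may be under-represented among the parasitaemic. Tables 6a and 6b assume that the study drugs reduce parasitaemia, so the chance of being typed also depends on the randomised arm.

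At stake are secondary outcome 7, the secondary objective on the genes, and the adjustment foreseen in Section 1.6. A child without parasitaemia has no genotype and drops out of any adjusted model.

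**Working it through.** **Inputs from the protocol.** Arm sizes are 610 (low/moderate site) and 320 (high site), 3,720 infants in total (Section 4.4). Parasite prevalence at 10 months, in the order placebo / mefloquine / Lapdap and SP, is 30 / 15 / 20% in Table 6a and 40 / 20 / 30% in Table 6b. Section 4.11 expects about 230 parasitaemic placebo samples.

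**Assumed inputs.** True carriage q, and the relative risk RR of parasitaemia in carriers. The protocol gives neither.

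**Step 1: the protocol's own count.** 610 + 320 = 930 placebo infants, and 930 × 0.25 = 232.5. This agrees with the stated figure of about 230. It is the only sample count given for molecular typing from trial samples, and it concerns parasite markers. No count is given for the host genes.

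**Step 2: children who would have a genotype from a 10-month survey** (no allowance for loss to follow-up)

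| Arm | Low site | High site | Total | Share of 930 |
|---|---|---|---|---|
| Placebo | 610 × 0.30 = 183 | 320 × 0.40 = 128 | 311 | 33% |
| Mefloquine | 610 × 0.15 = 91.5 | 320 × 0.20 = 64 | 155.5, about 156 | 17% |
| Lapdap | 610 × 0.20 = 122 | 320 × 0.30 = 96 | 218 | 23% |
| SP | 610 × 0.20 = 122 | 320 × 0.30 = 96 | 218 | 23% |

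The sum is 902.5, and 902.5 / 3,720 = 24%. About 76% of infants would have no genotype, and placebo would supply twice as many typed children as mefloquine.

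**Step 3: prevalence seen among parasitaemic children** = q·RR / (q·RR + 1 − q). With q = 15%:

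- RR 0.9: 0.135 / 0.985 = 13.7%
- RR 0.7: 0.105 / 0.955 = 11.0%
- RR 0.5: 0.075 / 0.925 = 8.1%
- RR 0.3: 0.045 / 0.895 = 5.0%
- RR 1.0: 15.0%, no bias

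At RR 0.5, true carriage of 10, 20 or 40% is seen as 5.3, 11.1 or 25.0%.

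**Step 4: comparison of arms** (assumed q = 20%)

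- If gene and drug act multiplicatively, with RR 0.5 and no interaction, carriage among the parasitaemic is 0.10 / 0.90 = 11.1% in every arm. A multiplicative interaction would show as a difference between arms and could be estimated.
- If carriers' risk is 10 percentage points lower in both arms, non-carrier risk at the low site is 0.30 + 0.2 × 0.10 = 0.32 on placebo and 0.15 + 0.02 = 0.17 on mefloquine. Carriage among the parasitaemic is then 0.2 × 0.22 / 0.30 = 14.7% on placebo and 0.2 × 0.07 / 0.15 = 9.3% on mefloquine, although randomisation made the arms equal.

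**Step 5: haemoglobin.** In an illustrative simulation, 20% were carriers, gene and drug each halved the risk of parasitaemia, and both acted on Hb only through parasitaemia. In all children the carrier difference was 0.12 g/dl and the drug effect 0.15 g/dl. Among parasitaemic children both were about zero. An analysis confined to the typed children would miss effects that exist in the trial population.

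**The case against.** The sentence in Section 4.12 describes laboratory methods and is not a sampling plan, and the word *only* does not appear in it. Section 1.6 names the study population as the target, so the restriction may be a drafting accident. That is fair, but the text still gives one DNA source and it is the wrong one for host genes. An equally possible reading borrows the Section 4.11 sample, parasitaemic control children at 10 months. No child on active drug would then be typed. The text does not settle this.

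A single survey may also understate the yield. Section 4.9 collects blood for molecular markers at visits clinically diagnosed as malaria, and ever-parasitaemic children are a larger, less selected group. Suppose 70% of non-carriers are ever infected (the high scenario under Table 1), with q = 15% and an infection rate ratio of 0.5. Then 1 − 0.3^0.5 = 45.2% of carriers are infected, and observed carriage is 0.0678 / (0.0678 + 0.595) = 10.2%, against 8.1% in Step 3. The bias shrinks but remains.

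Four stronger readings are tempting, and the protocol does not support them:

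- *Haemolysis in G6PD-deficient infants given Lapdap cannot be studied.* Section 4.8, if triggered, provides a case-control comparison that can estimate an odds ratio for Hb drop without requiring parasitaemia. It is conditional and confined to G6PD in the safety sample, so it gives neither population prevalence nor haemoglobin-gene data.
- *Prevalence is certain to be biased downwards.* That needs RR below 1. Section 1.6 makes it plausible but gives no figure.
- *Hardly anyone would be typed.* The under-one prevalences of 4% and 20% in Section 3 would give 610 × 0.04 + 320 × 0.20 = 88 placebo children. Those are survey figures for all infants under one, and the 20% comes from the site that Section 3.1 replaced. The protocol's own planning figures give about 230 to 311.
- *The main result is compromised.* The comparison of malaria incidence by randomised arm needs no genotype adjustment to be valid.

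**Conclusion.** The point holds as a conflict between the DNA source in Section 4.12 and the aims in Sections 1.6, 2.2 and 4.3. Followed as written, the rule leaves about three quarters of infants without a genotype at the 10-month survey, with typed shares of 33% on placebo and 17% on mefloquine. Prevalence is understated whenever carriers have a lower risk of parasitaemia: from 1.3 points at RR 0.9 to 10 points at RR 0.3, if true carriage is 15%. Genotype-adjusted comparison of the randomised groups would lose most of the trial. A multiplicative gene-by-drug interaction on parasitaemia remains estimable if parasitaemic children in all arms are typed.

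The counts rest on the prevalences in Tables 6a and 6b, the latter drawn up for the former high-transmission site. The size of the prevalence bias rests on assumed carriage and relative risk. One secondary outcome and one secondary objective are affected, and the primary comparison is not.

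**What to change.** In Section 4.12, limit the phrase about parasitaemic children to DHFR and DHPS. Add a sentence stating that G6PD and haemoglobin genes are typed in all randomised infants, or in a random sample drawn by arm and site, irrespective of parasitaemia, and give the planned number.

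The contact 1 filter papers are a natural source. Section 4.5 lists blood collection after the first dose, but this does not matter because dosing does not alter host genotype. Their stated purpose is parasite resistance, so consent and purpose must first be confirmed to cover host typing.

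Typing everyone needs more assays. A random sample of equal size does not: with 902 infants and 15% carriage the 95% half-width is 1.96 × √(0.15 × 0.85 / 902) = 2.3 percentage points, with no selection bias whatever the RR. If sampling fractions differ by site, the overall prevalence needs weighting. Genotype adjustment should then be described as an analysis within that sample. Table 8 gives one line of $10,000 for HPLC and SSOP together with no assay count, so the affordable number has to be agreed with the laboratory.
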